### **2.4.2 Secondary Endpoints:**

- Ventilation free days (VFDs) at day 28, defined as the total number of days that patient is alive and free of ventilation between randomisation and day 28 (censored at hospital discharge). Ventilation is considered as positive pressure ventilation, either invasive or non-invasive. Periods of assisted breathing lasting less than 24 hours for surgical procedures will not count against the ventilation free days calculation;
- Need of rescue administration of high-dose steroids or immune-modulatory drugs;
- Occurrence of switch from non-invasive to invasive mechanical ventilation during ICU-stay;
- Delay from start of non-invasive ventilation to switch to invasive ventilation;
- All-cause mortality at ICU discharge and hospital discharge;
- ICU free days (IFDs) at day 28, defined as the total number of days between ICU discharge and day 28. If death occurs during the ICU stay before day 28 the ICU free days calculation will be 0. The ICU readmission before day 28 after randomization will be considered;
- Occurrence of new infections from randomization to day 28; including infections by Candida, Aspergillus, Adenovirus, Herpes Virus e Citomegalovirus
- Occurrence of new organ dysfunction and grade of dysfunction during ICU stay. Organ dysfunction is defined as a Sequential Organ Failure Assessment (SOFA) score  $\geq 3$  occurring after randomization, grade of dysfunction is measured with SOFA score (see SOFA score in APPENDIX 4) daily from randomization to ICU discharge (censored at day 28);
- Objectively confirmed venous thromboembolism, stroke or myocardial infarction;
- Occurrence of major bleeding (safety end point), defined as transfusion of 2 or more units of packed red blood cells in a day, bleeding that occurs in at least one of the following critical sites [intracranial, intraspinal, intraocular (within the corpus of the eye; thus, a conjunctival bleed is not an intraocular bleed), pericardial, intra-articular, intramuscular with compartment syndrome, or retroperitoneal], bleeding that necessitates surgical intervention and bleeding that is fatal (defined as a bleeding event that was the primary cause of death or contributed directly to death);

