### **2.6 SAMPLE SIZE**

The target sample size is based on the hypothesis that the combined use of UHF and steroids versus the LMWH group will significantly reduce the risk of 28-day death. The overall sample size in this study is expected to be 210 with a randomization 1:1:1. Assuming an alpha of 2.5% (two tailed) and mortality rate in LMWH group of 50%, as indicated from initial studies of ICU patients, the study will have an 80% power to detect at least a 25 % absolute reduction in the risk of death between:

a) LMHW + steroids group and LMWH group

or

b) UHF + steroids group and LMWH group

The study has not been sized to assess the difference between LMHW + steroids group and UHF + steroids group, therefore the results obtained from this comparison will need to be interpreted with caution and will need further adequately sized studies to be confirmed.

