## **4.2 STATISTICAL METHODS**

### **4.2.1 Methods for statistical analysis**

All patients enrolled in the study will be entered in the full analysis set independently of his/her treatment time. The intention to treat population will be considered for primary analysis. A descriptive statistical analysis will be performed to describe every relevant variable. In general, categorical data will be presented using counts and percentages, whilst continuous variables will be presented using the number of patients, mean, standard deviation, median, minimum, and maximum. Denominators for calculation of percentages will be taken as the number of non-missing responses in the specified analysis population and treatment group unless otherwise stated, and percentages will be rounded to one decimal. Minima and maxima will usually be reported to the same level of accuracy as the raw data; means, medians and standard deviations will be presented to one further decimal place; standard errors (if presented) will be presented to 2 decimal places more than the raw data. 97.5 % confidence interval will be calculated for primary outcome and for the relevant secondary ones. All data recorded in the CRF will be listed. Distribution of SAPSII and SOFA score (total and for single organ) at admission, P/F ratio distribution at baseline and at day 3, biomarkers PCR, PCT and IL-6 P/F ratio distribution at baseline and at day 3 will be summarized.

The comparison between

1. LMHW + steroids group and LMWH group
2. UHF + steroids group and LMWH group

with binary outcomes will be performed by using Relative Risks (RRs), whereas for continuous data, the difference of means (DMs) will be used. Comparisons involving time to event data will be displayed by using Kaplan-Maier survival curves and summarised by Hazard Ratios (HRs).

All measures of association will be presented with their confidence intervals. A result will be considered as statistically significant if its p-values will be less than 0.025 (2.5%).

The analyses will be performed by using STATA software.

As the study has not been sized to assess the difference between LMHW + steroids group and UHF + steroids group, the results obtained from this comparison will be reported and will be interpreted with caution. The main analyses will not take into account the factors of stratification.

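### Section 4.2.1 calls any result with p<0.025 statistically significant, but that level was set for 28-day mortality in two contrasts and gives no protection across the secondary endpoints

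*Protocol*

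**What the plan says.** Protocol section 2.6 derives the sample size for 28-day death only: "Assuming an alpha of 2.5% (two tailed) and mortality rate in LMWH group of 50"%, and "the study will have an 80% power to detect at least a 25 % absolute reduction in the risk of death between" each steroid arm and the LMWH arm. The total follows: "The overall sample size in this study is expected to be 210 with a randomization 1:1:1".

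Section 4.2.1 names the same two comparisons, "LMHW + steroids group and LMWH group" and "UHF + steroids group and LMWH group". It gives methods for binary, continuous and time-to-event outcomes in general, and then states: "A result will be considered as statistically significant if its p-values will be less than 0.025 (2.5"%). Nothing in that sentence or around it confines the rule to mortality. The same section also carries the level over to secondary outcomes: "97.5 % confidence interval will be calculated for primary outcome and for the relevant secondary ones". It says separately that every measure of association will be given with a confidence interval. The only caution on interpretation concerns the comparison of the two steroid arms.

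Section 2.4.2 lists eleven bullets, two of them bleeding safety endpoints. The interim-analysis part of section 5.1 plans a look after 90 randomised patients, with action if survival differs significantly among the groups. It states no significance level for that look.

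**The concern.** A two-sided 2.5% level per comparison is what results from sharing 5% between two contrasts on one endpoint. Applied to every result, it looks like multiplicity control but provides none across endpoints.

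Read literally, section 4.2.1 would let a trial that is neutral on 28-day mortality report a statistically significant effect on ventilation-free days, ICU-free days, new infections or "Need of rescue administration of high-dose steroids or immune-modulatory drugs", and do so under its own prespecified rule. With some twenty such tests, one chance finding would not be unusual. What is at stake is which claims the trial may make from its secondary results.

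**Working it through.** **1. Where the 2.5% comes from.** Inputs from section 2.6: control mortality 0.50, treated mortality 0.50 − 0.25 = 0.25, two-sided alpha 0.025 (z = 2.2414), power 80% (z = 0.8416). With the pooled-variance formula and mean rate 0.375:

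n = [2.2414 × √(2 × 0.375 × 0.625) + 0.8416 × √(0.50 × 0.50 + 0.25 × 0.75)]² / 0.25²

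= [2.2414 × 0.68465 + 0.8416 × 0.66144]² / 0.0625 = 69.97, so 70 per arm and 3 × 70 = 210.

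This reproduces the plan's figure. A two-sided 5% level would need only 58 per arm. So 2.5% is the level used for each of two mortality contrasts.

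**2. What it achieves on one endpoint.** For two independent tests, 1 − 0.975² = 4.9%. With the shared LMWH arm (correlation 0.5 between contrasts), simulation gives 4.6%. Both figures assume a single final analysis.

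**3. Counting the secondary tests.** Leaving out the two bleeding endpoints, section 2.4.2 has nine bullets: ventilation-free days, rescue treatment, switch to invasive ventilation, delay to that switch, mortality at ICU and hospital discharge, ICU-free days, new infections, new organ dysfunction and its grade, and the thromboembolic composite. Splitting the two double bullets (mortality; organ dysfunction) gives eleven. Two contrasts make 18 to 22 tests. The process-of-care outcomes in section 2.4.3 are not counted, although the rule as worded covers them too.

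**4. Expected false positives.** If there is no true effect on any of these endpoints, the expected number is 18 × 0.025 = 0.45 to 22 × 0.025 = 0.55, whatever the correlation.

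**5. Chance of at least one.** If all 22 tests were independent, the chance would be 1 − 0.975²² = 42.7%. They are not independent, because the control arm is shared and the endpoints are related. A simulation (200,000 draws, three equal arms, normal test statistics, a common endpoint correlation, |z| > 2.241 in either contrast) gives:

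| Assumed endpoint correlation | 9 endpoints | 11 endpoints |
|---|---|---|
| 0 | 34.9% | 40.7% |
| 0.3 | 31.2% | 35.8% |
| 0.5 | 26.2% | 29.5% |
| 0.8 | 16.2% | 17.6% |

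The protocol gives no endpoint correlations, so these are assumptions and the result is a range of roughly 16% to 41%.

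**6. The interim look.** This matters for how a narrower rule should be worded. If p<0.025 were applied to mortality at 90 of 210 patients and again at the end, simulation gives about an 8.0% chance of at least one false mortality finding across the two contrasts, against 4.6% for the final analysis alone. Section 5.1 does not say that 0.025 is the interim level, so this is an illustration.

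**The case against.** The strongest objection is that hierarchies, corrections and exploratory labels for secondary endpoints are commonly left to the SAP, which is not at hand. That is right as far as it goes: their absence from the protocol is not a defect. The point here is different. The protocol states a decision rule and words it for every result. An SAP that confined significance to mortality would conflict with that sentence, so the sentence needs correcting in either case.

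It can also be said that the protocol already ranks its endpoints. It has one primary endpoint and one sample-size calculation, it links a change in practice to mortality alone, and 2.5% is stricter than the usual per-test 5%. This stands in part. The protocol nowhere promises 5% across the secondary endpoints, so the range above should not be presented as a breach of a stated guarantee. It measures how little the label would mean if applied as written.

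The model is also simple. ICU and hospital mortality overlap heavily, ventilation-free and ICU-free days both incorporate death, delay to invasive ventilation exists only in patients who switch, and the thromboembolic composite may be sparse. A single common correlation is an approximation, and some of these features would lower the figure.

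A reader might infer from the phrase about relevant secondary outcomes that the sponsor could choose what to report after seeing the data. The documents do not support this, because section 4.2.1 also says that all measures of association will be presented with confidence intervals. What is unclear is only the interval level for the secondary outcomes not deemed relevant.

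The open-label design, in which clinicians influence rescue use and some other outcomes, raises a question of bias. It is separate from multiplicity and adds nothing to the figures here.

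**Conclusion.** The concern holds as a fault in a stated rule. Section 4.2.1 extends to every result a threshold that was set for 28-day mortality in two contrasts. For 9 to 11 non-safety secondary endpoints in two contrasts, the chance of at least one false significant result is roughly 16% to 41%. This assumes no true effect on any of them, a shared control arm, endpoint correlations between 0.8 and 0, and endpoints that can all be tested.

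Two stronger readings should be avoided. A single figure of about 30% would need a correlation near 0.5 and all eleven endpoints equally testable, neither of which the protocol supplies. Nor should the 4.6% for mortality be read as showing that the primary comparison is fully protected, since it ignores the interim look. The sample size itself is correctly derived and is not in question.

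**What to change.** In section 4.2.1:

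- Limit the significance statement to 28-day mortality in contrasts 1 and 2. Set the level at 2.5% per contrast overall, with a final level that accounts for any efficacy test at the interim analysis in section 5.1, and not 2.5% at each look. The division between looks can be given in the SAP.
- State that secondary and process-of-care outcomes are reported as estimates with confidence intervals, without a claim of statistical significance. Alternatively, name one or two key secondaries and test them in fixed order within a contrast, only after a significant mortality result in that contrast.
- Report bleeding with unadjusted intervals, so that evidence of harm is not weakened.
- Align the two sentences on confidence intervals, so that the interval level for every secondary outcome is clear.

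The cost is a few sentences. Limiting the rule to mortality needs no extra patients or data. The sponsor gives up the option of calling a single secondary result significant. If an efficacy test is made at the interim, the final level falls below 2.5%. Because 70 per arm is the minimum for 80% power at 2.5% (69.97 before rounding), power should then be restated.

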## **2.0 METHODS: PARTICIPANTS, INTERVENTIONS AND OUTCOMES**

### **2.1 STUDY SETTING**

The study will involve 8 Italian Academic and non-Academic Intensive Care Units.

See list of centres in APPENDIX 1.

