## **2.4 OUTCOMES**

### **2.4.1 Primary Endpoint:**

- All-cause mortality at day 28.

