### **3.0 METHODS: ASSIGNEMENT OF INTERVENTIONS**

#### **3.1 Allocation and blinding**

A block randomisation will be used with variable block sizes (block size 4-6-8), stratified by 3 factors: Centre, BMI (<30; ≥30) and Age (<75 e ≥75). Central randomisation will be performed using a secure, web-based, randomisation system. The allocation sequence will be generated by the study statistician using computer generated random numbers. The attending physician, according to the protocol and the randomization, will note the inclusion of the patient in the study. Clinicians will receive all the instructions to attend the protocol and paper printed instructions will be distributed in the participating centres. The local coordinator will be responsible of the training and information of the personnel about the study protocol. The study is conceived as open-label: the patients and all the healthcare personnel will be aware of the group allocation.

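### Randomisation is stratified by centre, BMI and age, but the protocol fixes unadjusted main analyses: the stated power and error rate hold, yet recoverable power is given up if these factors predict death

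*Protocol*

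**What the plan says.** Section 3.1 (Allocation and blinding) describes the randomisation as "stratified by 3 factors: Centre, BMI (<30; ≥30) and Age (<75 e ≥75". Section 2.1 gives the number of sites: "The study will involve 8 Italian Academic and non-Academic Intensive Care Units". That makes 8 × 2 × 2 = 32 strata.

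The primary endpoint in section 2.4.1 is binary: "All-cause mortality at day 28". Section 4.2.1 compares each steroid arm with the LMWH arm, and the comparison "with binary outcomes will be performed by using Relative Risks (RRs"), at a 2.5% significance level with 97.5% confidence intervals. The same section ends with: "The main analyses will not take into account the factors of stratification". It gives no reason and describes no adjusted or stratified analysis.

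This is a choice that the protocol makes, not a detail left to a statistical analysis plan. An analysis plan that adjusted the primary comparison would contradict the protocol.

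**The concern.** Stratified blocks remove from the treatment comparison some of the between-arm variation that the strata would otherwise cause. An unadjusted standard error is computed as if that variation were still there. When the strata predict the outcome, the standard error is therefore larger than the true sampling variability, the test rejects less often than its nominal level, and part of the precision that the design bought does not reach the p-value or the interval.

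What is at stake is efficiency, not validity. The trial is sized for a large effect at just 80% power. All three factors are recorded at randomisation, so using them costs nothing in patients or data.

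**Working it through.** **1. The plan's own figure.** Inputs from section 2.6: two-sided alpha 0.025 per comparison, mortality 50% v 25%, power 80%, 210 patients allocated 1:1:1. With pooled variance under the null and no continuity correction:

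n per arm = [z(0.9875)·√(2·0.375·0.625) + z(0.80)·√(0.50·0.50 + 0.25·0.75)]² / 0.25²
= [2.241·0.6847 + 0.842·0.6614]² / 0.0625 ≈ 70, so 210 in total.

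Power at 70 per arm is 80.0%. The sample size is that of an unadjusted test, so sample size and planned analysis agree with each other.

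**2. What stratification does to that test.** The protocol gives no prognostic strength, so it is assumed over a range. Simulation A: 6,000 trials per row, 210 patients, 32 strata, equal centres, BMI ≥30 in 40%, age ≥75 in 15%, blocks of 3/6/9. The adjusted analysis is a risk difference with main effects of centre, BMI and age and a robust standard error. Monte Carlo standard error is about 0.2 points for type I error, √(0.025·0.975/6000), and 0.5 points for power, √(0.8·0.2/6000).

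| Assumed strength (SD of centre log-odds / BMI OR / age OR) | Null rejection, unadjusted | Null rejection, adjusted | Null SE: model v true | Power, unadjusted | Power, adjusted |
|---|---|---|---|---|---|
| None (0 / 1 / 1) | 2.53% | 2.68% | 0.0840 v 0.0851 | 79.8% | 79.4% |
| Mild (0.3 / 1.22 / 2.01) | 2.32% | 2.62% | 0.0840 v 0.0840 | 80.8% | 82.1% |
| Moderate (0.5 / 1.35 / 3.32) | 2.32% | 3.02% | 0.0840 v 0.0823 | 81.4% | 84.1% |
| Strong (0.8 / 1.65 / 6.05) | 1.55% | 2.85% | 0.0840 v 0.0790 | 81.4% | 87.4% |

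In the strong row the standard error is 0.0840/0.0790 = 1.063 times too large. The effective critical value is then 2.241·1.063 = 2.383, a two-sided level of about 1.7%, in line with the simulated 1.55%.

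**3. Removing the part of the gain that comes from a liberal test.** Near 80% power, one extra point of alpha is worth about φ(0.84)/(2·φ(2.24)) ≈ 4.3 points of power. In the moderate row the excess of 0.52 points explains 0.52·4.3 ≈ 2.2 of the 2.7 points gained. In the strong row 0.35·4.3 ≈ 1.5 of the 6.0 points are explained this way.

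Simulation B (5,000 trials per scenario) therefore used a linear risk-difference model with a model-based standard error, whose null rejection was 2.2 to 2.6%. Power, unadjusted v adjusted:

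- none: 80.1% v 79.5%
- mild: 80.9% v 81.0%
- moderate: 81.0% v 82.5%
- strong (age OR 4.5, BMI OR 1.5, centre SD 0.5): 80.8% v 84.4%

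Unadjusted type I error was 2.5%, 2.4%, 2.2% and 1.8%. A further run of 2,500 trials per cell, which did not reach the strong case, gave a change of 0 to −1 points with non-prognostic factors, −1 to +1 if mild and about +2 if moderate (81.1% v 83.0%).

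**4. Block sizes.** Section 3.1 says: "A block randomisation will be used with variable block sizes (block size 4-6-8"). Blocks of 4 and 8 cannot be split equally over three arms. That is a separate matter, but it makes balance within strata weaker than in simulations A and B. With blocks of 4/6/8 (leftover places at random) or 6/9/12, 5,000 trials per cell, unadjusted type I error was 2.6 to 2.9% (mild), 2.4 to 2.6% (moderate) and 1.8 to 2.2% (strong).

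**5. How to adjust.** In the same runs a standardised logistic analysis rejected a true null in 3.7 to 4.1% of trials with a plain robust standard error and in 2.9 to 3.3% with a degrees-of-freedom correction. A Cochran-Mantel-Haenszel test on all 32 cells (140/32 ≈ 4.4 patients per cell in a pairwise comparison) lost power in simulation A: 75.8% v 79.8% unadjusted with non-prognostic factors, and 77.6% v 80.8% in the mild case.

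**The case against.** The strongest reply is that the unadjusted analysis is prespecified, transparent and consistent with the sample size, and that any error it makes is on the safe side. That stands. Three stronger readings are tempting, and the documents do not support them.

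- *The trial falls short of its 80% power.* It does not. The 210 patients come from the unadjusted formula, and simulated unadjusted power is about 80 to 81% throughout. Power is lost only relative to an adjusted analysis.
- *The intervals and test are conservative as planned.* In the non-prognostic, mild and moderate cases the unadjusted error rate lies within about two Monte Carlo standard errors of 2.5%. Clear conservatism needs strongly prognostic factors, and the protocol gives no figure for their strength.
- *The benefit of stratifying is lost.* Protection against chance imbalance remains and the estimate itself is more precise: in simulation A its true standard error falls from 0.085 to 0.079. Only the reported standard error fails to reflect this.

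It is also fair to object that adjustment does not bring the error rate to 2.5% by itself. With a plain robust standard error the adjusted test can exceed its level by more than the planned test falls below it. That objection decides the form of the remedy, but not whether to adjust: with a model-based standard error the size held and the gain remained in the moderate and strong cases.

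Finally, the reference to main analyses leaves room for adjusted sensitivity analyses. Such analyses would not recover the power, because the primary conclusion would still rest on the unadjusted comparison.

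**Conclusion.** The point holds as a matter of efficiency. The protocol stratifies on three factors and, without a stated reason, bars the main analyses from using them. The planned test is valid, reaches its stated power and does not inflate false positives. What it forgoes is about nil if the factors are weak, 1 to 2 points of power if moderate and 3 to 6 points if strong. Type I error falls to about 1.6 to 2.2% only in the strong case.

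These sizes rest on assumed prognostic strengths, assumed shares of older and obese patients, and mostly on blocks divisible by three. Weaker balance under the stated block sizes would reduce the conservatism. No positive conclusion of the trial is threatened.

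**What to change.** Replace the sentence in section 4.2.1 with a prespecified primary analysis:

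- a marginal relative risk and risk difference for each steroid arm against LMWH, adjusted for main effects of age group, BMI group and centre;
- one parsimonious rule for centre, written down in advance (for example, pooling centres below a stated size), and no stratification on all 32 cells;
- a variance method shown by simulation, under the block scheme actually used, to hold the 2.5% level. A model-based standard error did so in the runs above. A degrees-of-freedom correction is a candidate but ran at 2.9 to 3.3% in one set of runs, so it needs that check. A plain robust standard error should not be used;
- the unadjusted relative risk kept as a supportive analysis.

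The choice should be fixed before any outcome data are seen, hence before the interim analysis after 90 randomised patients (section 5.1).

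The cost is protocol and analysis-plan wording, a short simulation and a few lines of Stata; no new data or patients are needed. The statistical downside is up to about 1 point of power if the factors turn out not to be prognostic.
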